#### Blinding (masking)

During intervention period: Due to the nature of the study, the assignment of infants to control arm or intervention arm cannot be blinded to the clinical staff (care providers). For infants in the control arm, the monitor screen will be blinded to the clinical team, this will be performed using an opaque cover over the monitor screen. For each monitor, it is possible to silence the low and high alarm, but keep the alarm ON for displacement of the sensors when the sensors are not making contact with the skin. Alarms for the range of cerebral tissue oxygenation (65-90) will be turned off and alarms for displacement/dislodgement of the sensors will remain active. Clinical staff (bedside nurse) will be provided with data collection sheet to determine the frequency of alarms and sensor repositioning during each shift for both arms.

Post-intervention period: Data analysts, other site personnel/investigator, outcome assessors and manuscript writers will be blinded to the intervention.

#### 6.5 STUDY METHODOLOGY

Enrolment will occur after birth of the baby. After enrolment, infants will be randomised to either control group or intervention group. For all enrolled babies, monitoring of cerebral oxygenation will be commenced by placement of a non-adhesive probe on the fronto-parietal region of the forehead within 6 hours of birth and monitoring will be continued for 5 days.

For the Intervention group:

For the intervention group, the cerebral oxygenation reading is visible and the baby will be treated according to a dedicated clinical guideline when the cerebral oxygenation is outside the range of 65%-90% as shown in Figure 1 and Figure 2. The sensor site will be inspected based on the unit's practice of skin assessment to ensure correct sensor placement and skin integrity.

**Clinical algorithm for cerebral hypoxia triggered when cerebral oxygenation (CrSO2) is < 65% (Figure 1)**

When Cerebral oxygenation (CrSO2) is < 65% potential causes could include inaccurate sensor placement, low arterial oxygen saturation (20-23), reduced cerebral blood flow (23-38) and/or reduced haemoglobin concentration in circulating blood (39-43).

**Figure 1: Clinical algorithm for cerebral tissue hypoxia**

Important causes of cerebral hypoxia (low CrSO2) include (but not limited to) conditions that decrease O2 delivery to the brain such as low SpO2, systemic hypotension, haemodynamically significant ductus arteriosus, hypocarbia and/or anaemia).

If no change to cerebral CrSO2 from sensor repositioning, and CrSO2 is consistently < 65% then check for the following (perform one change at a time and reassess within 30 minutes of making the change)

- Low peripheral oxygen saturation (SpO2): if below normal or in the low normal range then aim to bring it back to normal range by performing maneuvers such as increasing FiO2 and /or mean airway pressure.
- Abnormal cardiovascular status: presence of poor systemic perfusion and /or haemodynamically significant patent ductus arteriosus.
  - ✓ if clinical (capillary refill time ≥ 3 seconds or hypotension on non-invasive or invasive blood pressure measurement), or
  - ✓ biochemical (elevated serum lactate) or
  - ✓ echocardiographic signs (low cardiac output and/or low SVC flows) of poor systemic perfusion then consider administering a bolus of normal saline (10ml/kg) and /or inotropes.
  - ✓ Presence of haemodynamically significant patent ductus arteriosus (based on echocardiogram), consider medical treatment.
- Low PCO2 level (transcutaneous or capillary/arterial blood gas): if below normal or low normal range, then aim to normalize by adjusting the mean airway pressure and / or minute ventilation.
- Low haemoglobin level: if the most recent Hb is low consider packed red cell transfusion.

If any of the standard parameters such as blood pressure, serum lactate, SpO2 are deranged, clinician should target their correction despite CrSO2 levels (even if they are in the normal range).

**Clinical algorithm for cerebral hyperoxia triggered when cerebral oxygenation (CrSO2) is > 90% (Figure 2)**

When cerebral oxygenation (CrSO2) is > 90% potential causes could include inaccurate sensor placement, high arterial oxygen saturation (9-12, 20, 21, 44-47), increased cerebral blood flow (24, 25, 35, 38) , and/or hypoglycaemia (48, 49).

**Figure 2: Clinical algorithm for cerebral hyperoxia**

Important causes of cerebral hyperoxia (high CrSO2) include (but not limited to) conditions that increase O2 delivery to the brain such as high SpO2, hypercarbia, systemic hypertension, and/or hypoglycemia.

If no change to cerebral CrSO2 from sensor repositioning, and CrSO2 is consistently >90% then check for the following (perform one change at a time and reassess within 30 minutes of making the change)

- High SpO2: If above normal or in the high normal range, aim to bring it back to normal range by performing manoeuvres such as decreasing FiO2 and / or MAP.
- High PCO2 level (transcutaneous or capillary/arterial blood gas): if above normal or high normal range, then aim to normalize by adjusting the mean airway pressure and / or minute ventilation.
- Abnormal cardiovascular status: if hypertensive and receiving inotropes, considering weaning and/or ceasing inotropes.
- Hypoglycemia: if blood glucose level < 2.6 mmol/L, then increase glucose intake to maintain normal eu-glycaemia.

If no cause for high cerebral rSO2 identified, then continue close clinical assessment.

**Control group**

For the Control group, cerebral oxygenation reading is NOT visible and the baby will be treated according to standard clinical practice. We will perform blinded NIRS monitoring (we will cover the monitor) and the information will not be available to clinicians to act upon.

**Modifications**

Intervention will be discontinued if requested by parents.

**Adherence**

In response to an alarm (for intervention and control group), an event will be marked by the bedside clinical team on the NIRS monitor. From the Response To Alarm form, NIRS data and medical records observation chart, we will ascertain adherence to the study algorithm and

actions performed. Research nurse/local PI will conduct compliance audit for both groups during the study.

For the intervention group: A bedside “Response to Alarm” form will be made available for staff to prospectively record actions performed for low &/ high cerebral oxygenation alarms during their shift to ensure compliance to the clinical algorithm as well as event mark in response to the alarm on the NIRS monitor.

Nursing and medical staff will receive education prior to study commencement on the application of NIRS sensors, skin care during monitoring period, measures to consider when there is cerebral hypoxia and/or cerebral hyperoxia. Bedside flowcharts will be available for staff to perform changes to clinical management. A laminated chart will be placed on the crib to remind staff of NIRS target range as well as a flow chart suggesting possible reasons for cerebral hypoxia/hyperoxia and suggested interventions.

For the control group: A bedside “Response to alarm” form will be made available for staff to record prospectively actions performed for sensor contact alarms during their shift to report accuracy and vigilance of recordings as well as place an event marker in response to the poor patient contact alarm on the NIRS monitor. We will have a laminated chart specifying treatment ‘as per medical officer’s instructions’ for the control group.

#### Concomitant care

There are no restrictions on concomitant medications; infant care will be as per the local NICU practice.

### Outcomes

| Tool                 | Outcomes                                                                                                                                            | Time points                                                                   |
|-----------------------------|------------------------------------------------------------------------------------------------------------------------------------------------------------|--------------------------------------------------------------------------------------|
| Cerebral NIRS monitors      | Burden of hypoxia and hyperoxia expressed as percentage time spent < 65% and > 90%.                                                                        | First 5 days of monitoring period                                                    |
| Medical records             | Mortality rates                                                                                                                                            | Prior to home discharge                                                              |
| Cerebral imaging            | Evidence of brain injury on cranial ultrasounds and MRI brain (when performed for clinical reasons)                                                        | Prior to home discharge                                                              |
| Medical records             | Presence of neonatal morbidities (chronic lung disease, necrotizing enterocolitis, retinopathy of prematurity)                                             | Prior to home discharge                                                              |
| Neuro-developmental testing | 

General movement assessment

Cognition, motor and language domain scores on Bayley Scales of Infant

 | At 4 months (CGA)

At 12 months (CGA), 18-24 months (CGA), and 5 years of age. |

|                                 |                                                                                                                                  |                                   |
|---------------------------------|----------------------------------------------------------------------------------------------------------------------------------|-----------------------------------|
|                                 | and Toddler development 
 
• Wechsler Preschool and Primary Scale of Intelligence
 
 | 5 years of age                    |
| Pulse oximeter, medical records | pulse oximetry (SpO 2 ), heart rate (HR) and blood pressure                                                           | First 5 days of monitoring period |
| Medical records                 | Serious and non-serious adverse reactions                                                                                        | First 5 days of monitoring period |

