| Bronchopulmonary Dysplasia, n (%)                      | 41/72 (57)            | 28/60 (47)        | 1.27 (0.94 to 1.50) |                      | 0.20               |
| Retinopathy of Prematurity, n (%)                      | 14/86 (16)            | 8/80 (10)         | 1.64 (0.75 to 3.00) |                      | 0.20               |

Currently, SafeBoosC III study is ongoing which is a large, pragmatic trial in extremely preterm babies to examine if cerebral oximetry combined with a treatment guideline can reduce the risk of death or severe brain injury at 36 weeks of age.

(<https://www.rigshospitalet.dk/english/departments/juliane-marie-centre/departments-of-neonatology/research/SafeboosC-III/Sider/default.aspx>).

There are no adequately powered RCT's investigating stability of cerebral oxygenation and impact on neurodevelopmental outcomes (until 5 years of age). While it is very encouraging that CP rates for preterm infants have recently declined in Australia, there is still much to do in preventing brain injury in extremely preterm infants especially preventing brain injury at birth and in the first few days of life. Evidence supports hypoxia contributing to mortality as well as brain injury.

There is an urgent need for a safe and effective non-invasive clinical approach incorporating cerebral NIRS monitoring, with good evidence to support its use(18). However, there are no studies of this nature, investigating the effects of targeted cerebral oxygen monitoring on mortality before hospital discharge and long-term neurodevelopment.

Additionally, it is important to note, in Australia and New Zealand, the standard practice for all premature babies who are born before 29 weeks gestation, is to have the following:

- Serial cranial ultrasounds
- MRI brain if clinical concerns or cranial ultrasound evidence of brain injury
- Regular neuro-developmental assessments till 5 years of age.

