
386

387

388

389

390

391

392

393

394

396 **10.** Flowchart or table specifying visits, interventions and other relevant details

|                                                  |           |            | STUDY PERIOD |    |    |    |    |    |    |    |    |
|--------------------------------------------------|-----------|------------|--------------|----|----|----|----|----|----|----|----|
| TIMEPOINT                                        | Enrolment | Allocation | T1           | T2 | T3 | T4 | T5 | T6 | T7 | T8 | T9 |
| ENROLMENT:                                       |           |            |              |    |    |    |    |    |    |    |    |
| Eligibility screening                            | X         |            |              |    |    |    |    |    |    |    |    |
| Informed consent                                 | X         |            |              |    |    |    |    |    |    |    |    |
| Allocation                                       |           | X          |              |    |    |    |    |    |    |    |    |
| INTERVENTION:                                    |           |            |              |    |    |    |    |    |    |    |    |
| Intervention group                               |           |            | X            |    |    |    |    |    |    |    |    |
| Control group                                    |           |            | X            |    |    |    |    |    |    |    |    |
| ASSESSMENTS:                                     |           |            |              |    |    |    |    |    |    |    |    |
| Skin Integrity Tool                              |           |            | X            |    |    |    |    |    |    |    |    |
| Record of response to alarm                      |           |            | X            |    |    |    |    |    |    |    |    |
| Cranial ultrasounds                              |           |            |              | X  | X  |    |    |    |    |    |    |
| Data download of overnight pulse oximetry (once) |           |            |              |    |    | X  |    |    |    |    |    |
| Day sleep study (once)                           |           |            |              |    |    | X  |    |    |    |    |    |
| MRI brain (where performed)                      |           |            |              |    |    |    | X  |    |    |    |    |

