### *Secondary outcomes*

- Newborn mortality rates prior to home discharge
- Brain injury based on cerebral imaging prior to home discharge
- Neonatal morbidities (chronic lung disease, necrotizing enterocolitis, retinopathy of prematurity) prior to home discharge

- Physiological functions (observation of pulse oximetry) at 36-37 weeks PMA.
- Sleep architecture (based on sleep study) at 36-37 weeks PMA.
- Motor performance assessment (General movements assessment) during NICU stay and at 4 months corrected age follow up.
- Neuro-developmental outcomes until 5 years of age.
- Measurement of physiological functions (heart rate, pulse oximetry, blood pressure) in the first 5 days.

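### The brain-injury outcome includes MRI done only on clinical indication, by staff who may know the arm, so detection can differ between arms in an unknown direction

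*Combined protocol and SAP*

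**What the plan says.** **Outcome.** The SAP lists "Brain injury based on cerebral imaging prior to home discharge" among the secondary outcomes. Protocol Section 5.4 labels the secondary outcomes exploratory. The outcomes table in protocol Section 6.5 names two sources for it: cranial ultrasound and "MRI brain (when performed for clinical reasons".

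**Who is imaged.** Section 6.2 (item 5B) describes ultrasound as routine for all premature babies. The visit table in Section 6.2 places it at T2 (first week) and T3 (32 weeks PMA or 6 weeks after birth). The same table shows "MRI brain (where performed" at T5 (37–40 weeks PMA). Section 4.3 gives Australian and New Zealand practice as "MRI brain if clinical concerns or cranial ultrasound evidence of brain injury". No MRI rule is stated for the US site.

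**Who knows the arm.** Under Blinding in Section 6.4, allocation "cannot be blinded to the clinical staff (care providers". Intervention-arm staff see the readings and respond to range alarms. For controls the screen is covered and those alarms are off. For the period after the intervention the protocol states: "Data analysts, other site personnel/investigator, outcome assessors and manuscript writers will be blinded to the intervention". The SAP's blinding paragraph names only the statistician and the neurodevelopment assessors.

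**Analysis.** The SAP compares the other outcomes between arms by GEE, without imputation. Its only planned sensitivity analyses split the primary burden outcome into hypoxia and hyperoxia. Neither document plans an ultrasound-only analysis or a report of MRI rates by arm.

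**The concern.** A between-arm comparison of detected injury is fair only if both arms are looked at equally hard. Ultrasound meets that condition because every baby has it on a common schedule. MRI does not, because it depends on a clinical decision. Staff know the arm during the five days, and allocation itself gives one arm's staff information that the other's lack. Either could feed into what counts as a clinical concern.

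If babies with clear ultrasounds are sent for MRI more often in one arm, more MRI-only lesions will be found there even when true injury is equal. The planned GEE comparison would carry that difference into the result. Since scan rates by arm are not reported, a reader could not see that it had happened.

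The result will inform a larger trial. Section 11.2 also allows participants' information to be considered for use in that trial. Added babies reduce random error but do not reduce this kind of bias.

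**Working it through.** The plan states no rate, sample size or power for brain injury, so it has no figure of its own to reproduce. The 47 per group in Section 9.1 concerns the burden outcome only.

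**Step 1: which MRIs matter.** Treat the outcome as yes/no over all imaging.
- A baby positive on ultrasound already counts, so an MRI prompted by that finding does not change the classification.
- A baby negative on ultrasound can change from no to yes only through an MRI done for clinical concern.

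The bias therefore comes only from the second group.

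**Step 2: size under assumed rates.** Suppose true injury and ultrasound-prompted MRI are equal in the two arms. Then

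false difference = (difference between arms in the share of babies given MRI) × (share of the extra scans showing injury not seen on ultrasound).

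The documents give neither quantity. The values below are assumptions.

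| MRI rate, one arm v the other | Yield of extra scans | False difference | Babies per arm of 50 |
|---|---|---|---|
| 40% v 30% | 10% | 0.10 × 0.10 = 1.0 point | 0.5 |
| 40% v 25% | 30% | 0.15 × 0.30 = 4.5 points | 2.25 |
| 50% v 25% | 30% | 0.25 × 0.30 = 7.5 points | 3.75 |

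**Step 3: cross-check in ultrasound-negative babies only.** Assume 18% are positive on ultrasound in each arm. Let q be the share of ultrasound-negative babies with an MRI-only lesion. Then the false difference = (1 − 0.18) × q × (difference in MRI rate among ultrasound-negative babies).
- Scanned 40% v 20%: q = 10%, 20%, 30% gives 1.6, 3.3, 4.9 points.
- Scanned 60% v 20%, a deliberately wide gap: 3.3, 6.6, 9.8 points.
- Scanned equally: 0.
- Rates swapped to 20% v 40%: −1.6, −3.3, −4.9 points.

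The sign depends entirely on which arm is scanned more.

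**Step 4: scale.** With 50 per arm and an assumed rate of 18%, the standard error of the difference, ignoring twin clustering, is √(2 × 0.18 × 0.82 / 50) = 0.077, or 7.7 points. The step 2 scenarios all lie within one standard error. In the earlier phase II trial of NIRS-guided treatment (Section 4.3), severe injury differed by 23.4 − 12.5 = 10.9 points. That figure is severe injury on ultrasound, so it is a rough yardstick and not a like-for-like comparison.

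**The case against.** Several points on the other side are sound.

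- **Two routes to MRI.** A reader might infer that every MRI in the trial is open to this bias. Section 4.3 does not support that. Scans prompted by ultrasound injury add little to a yes/no outcome, which leaves only the clinical-concern route.
- **Direction.** A reader might infer that visible low readings would lead to more MRI, and so more detected injury, in the intervention arm. The documents do not show this. The treatment algorithms in Section 6.5 mention no brain imaging. The trial expects the intervention to halve the burden, so staff may see reassuring readings and scan less. Control staff, with no readings, may scan more.
- **Timing and blinding.** MRI is at 37–40 weeks PMA. For a baby born before 29 weeks that is at least about 7 weeks after monitoring stops. The protocol's post-intervention clause also lists other site personnel. Both may weaken knowledge of the arm. Neither removes it: the clause does not clearly cover the treating clinicians who order scans, and staff who already know the allocation cannot be made unaware of it.
- **Combination not spelled out.** No passage states a combined yes/no score. Even so, both documents define one outcome on cerebral imaging, the protocol table includes MRI in it, and no ultrasound-only version is planned.
- **Importance.** The outcome is exploratory, the trial is sized for burden, and in the step 2 scenarios the bias is within one standard error. The primary outcome is not affected.

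These points limit the weight of the concern. Central reading does not answer it, because it governs how scans are interpreted and not who is scanned.

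**Conclusion.** The concern holds in a limited form. As planned, the brain-injury comparison can be biased by arm-dependent MRI ordering in ultrasound-negative babies, and nothing in either document would prevent or reveal it. The documents show that detection can differ by arm. They do not show that it will, or in which direction.

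The size cannot be estimated from the documents. The three step 2 scenarios give about 1 to 8 percentage points, or roughly 0.5 to 4 babies per arm of 50. The more extreme gap in step 3 reaches 9.8 points, and equal scanning gives zero. All of this assumes equal true injury, an outcome scored yes/no over all imaging, and scan rates and yields that the documents do not supply. For an exploratory outcome this is a worthwhile, inexpensive correction and no threat to the trial's main conclusion.

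**What to change.** Amend both the SAP and the outcomes table in protocol Section 6.5:

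1. Base the between-arm brain-injury comparison on the scheduled cranial ultrasounds at T2 and T3, read centrally. State in the SAP that the imaging readers are blind to arm, since its blinding paragraph does not name them.
2. Describe MRI findings by arm, with the number of babies scanned and the reason for each scan (clinical concern or ultrasound finding).
3. Show the all-imaging result as a supplementary analysis.

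This needs no new scans and leaves clinical decisions about imaging unchanged. It does require a protocol amendment as well as SAP wording, and a recorded reason for each MRI.

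The price is some lost sensitivity. Injury seen only on MRI leaves the main comparison. So does injury first seen on an ultrasound after T3, since Section 6.3 has cranial imaging continuing through the admission. Both would still appear in the supplementary and descriptive results.
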